#### Population Pharmacokinetic Analysis

Population pharmacokinetic analyses will be performed using nonlinear mixed regression models with the software program NONMEM (Icon Development Solutions). This approach allows for the characterization of the average pharmacokinetic profile of PKI from data pooled over all sampled individuals and the quantification of inter- and intraindividual variability. This approach allows us to analyze sparse (few drug concentrations per patient) and unbalanced data. The built models integrate active metabolites when appropriate. The impact of potential sources of variability will be evaluated using linear and nonlinear functions.

#### Relationships Between PKI Exposure, Efficacy, and Toxicity

The correlation between PKI exposure and efficacy will be explored using Cox regression analysis of progression-free survival. The correlation between PKI exposure and toxicity will be explored by pharmacokinetic and pharmacodynamic models using the software program NONMEM or by logistic regression analysis. Receiver operating characteristic analyses will be used to evaluate the best exposure threshold to predict clinical outcomes and performance (in terms of area under the receiver operating characteristics curve and sensitivity and specificity).

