#### Pharmacokinetic and Pharmacodynamic Study

It has been empirically determined that at least 50 patients with several samples per PKI are necessary to characterize drug pharmacokinetics and variability.

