## Results

The first patient was included in May 2015. Until June 2021, 262 patients have participated in at least one part of the study (250 patients have given at least one blood sample, and 130 have been included in the adherence study). In June 2021, 51 patients treated with palbociclib have provided at least one blood sample, and the adherence study currently includes 43 participants with breast cancer, which corresponds to most of the included participants. Moreover, so far, at least one blood sample has been collected from patients treated with 31 different PKIs and their combination (Multimedia Appendix 4).

Data collection is in process, and the final analysis will be performed in 2022. The results of the study will be submitted to local, national, and international conferences and to peer-reviewed open access journals for publication.

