### Limitations of the Study

This study has some limitations. First, the adherence data will be collected over 12 months, a time frame during which several stops and breaks in the treatment regimen can occur. This will be a challenge for data analysis; however, the adherence team and the statistician, who will perform the analysis, have already dealt with this kind of data and are experts in this field [14]. Second, we expect some variability in the frequency of adherence visits among participants. Indeed, the adherence interviews are scheduled after each patient’s clinical appointment, and the frequency can vary from a quarterly to a monthly visit depending on the organization of the clinic and the severity of the patient’s disease. Third, the use of an electronic monitor can introduce a Hawthorne effect during the first 6 weeks of the study, which disappears afterward [40]. This effect is explained by the fact that patients who know they are being observed may improve their usual medication behavior. The impact of this effect will be explored in the analysis. Fourth, the number of blood samples may not be sufficient to initiate a population pharmacokinetic analysis for each monitored PKI. All limitations will be considered while analyzing the results and will be detailed in the final publication.

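### The exposure threshold chosen by ROC analysis, and its sensitivity and specificity, appear to come from the same patients without internal validation, so both measures will be moderately optimistic and the cut-off imprecise at about 50 patients per drug (minor)

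*Protocol article*

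**What the plan says.** Under *Relationships Between PKI Exposure, Efficacy, and Toxicity*, the protocol article plans three things. Exposure is related to efficacy: "The correlation between PKI exposure and efficacy will be explored using Cox regression analysis of progression-free survival". Exposure is related to toxicity by pharmacokinetic-pharmacodynamic models or logistic regression. Then a threshold is sought: "Receiver operating characteristic analyses will be used to evaluate the best exposure threshold to predict clinical outcomes and performance", with performance given "in terms of area under the receiver operating characteristics curve and sensitivity and specificity". The abstract repeats the ROC plan in shorter form. Neither place mentions a validation sample, cross-validation, bootstrap or any other allowance for the search.

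The only sample size given for this part, under *Sample Size*, is that "at least 50 patients with several samples per PKI are necessary to characterize drug pharmacokinetics and variability". Under *Results*, the one drug with a stated count stands at that level: "51 patients treated with palbociclib have provided at least one blood sample" as of June 2021. The 250 patients sampled by then were spread over 31 PKIs and their combinations.

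**The concern.** Choosing the best threshold means searching all possible cut-offs and keeping the one that separates events from non-events most favourably in the data at hand. Part of that separation is chance. Sensitivity and specificity read off at the winning cut-off in the same patients include the chance part, so on average they exceed what the cut-off would achieve in new patients. The position of the cut-off also varies widely from sample to sample.

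The *Background* section wants to define therapeutic targets for drug monitoring, and the conclusions look ahead to individual dosage. A threshold published with uncorrected performance and no interval could be taken up as a target on firmer evidence than the data provide, even where exposure predicts little.

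**Working it through.** The article states no ROC performance figure, and its 50 per PKI is an empirical rule without a formula. There is thus no figure to reproduce, and the size of the optimism was simulated.

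**Inputs from the article:** about 50 patients per drug (the stated minimum; 51 on palbociclib); a best threshold chosen by ROC; AUC, sensitivity and specificity reported.

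**Assumed, because the article gives none:** a threshold sought separately for each drug; event share 20%, 30% or 50%; true AUC 0.50 to 0.80; cut-off maximising the Youden index J = sensitivity + specificity − 1; normal exposure with equal variance (SD 1) in both outcome groups.

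**Method.**
1. Set the distance between group means to d = √2 · Φ⁻¹(AUC). For AUC 0.70, d = 1.414 × 0.524 = 0.74. The best attainable index is 2Φ(d/2) − 1 = 0.289.
2. Draw a sample, find the cut-off t with the largest J, and record its apparent sensitivity and specificity.
3. Compute the true values of that same cut-off: sensitivity 1 − Φ(t − d), specificity Φ(t).
4. Average over 6,000 samples per cell. Optimism is apparent minus true.

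**Results at n = 50.**

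| Event share | True AUC | Sensitivity, apparent / true (difference) | Specificity, apparent / true (difference) | Mean sample AUC |
|---|---|---|---|---|
| 20% | 0.50 | 0.693 / 0.534 (0.159) | 0.506 / 0.466 (0.040) | 0.501 |
| 20% | 0.70 | 0.764 / 0.623 (0.141) | 0.666 / 0.632 (0.034) | 0.700 |
| 20% | 0.80 | 0.823 / 0.696 (0.127) | 0.746 / 0.716 (0.030) | 0.802 |
| 30% | 0.50 | 0.638 / 0.514 (0.124) | 0.536 / 0.486 (0.050) | 0.500 |
| 30% | 0.70 | 0.734 / 0.629 (0.105) | 0.674 / 0.630 (0.044) | 0.700 |
| 30% | 0.80 | 0.796 / 0.702 (0.094) | 0.754 / 0.715 (0.039) | 0.799 |
| 50% | 0.50 | 0.646 / 0.564 (0.082) | 0.512 / 0.436 (0.076) | 0.500 |
| 50% | 0.70 | 0.723 / 0.656 (0.067) | 0.673 / 0.605 (0.068) | 0.700 |
| 50% | 0.80 | 0.796 / 0.737 (0.059) | 0.741 / 0.682 (0.059) | 0.799 |

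Over the grid, sensitivity is too high by about 0.06-0.16. Specificity is too high by 0.03-0.08 when the cut-off is placed midway between neighbouring observations. A repeat at n = 51 with the cut-off at the lower of the two neighbours takes the upper end to about 0.09. In relative terms the factors are 1.08-1.30 for sensitivity and 1.04-1.18 for specificity. The mean sample AUC matches the true AUC.

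**Cut-off precision at n = 51.** The sampling SD of the chosen cut-off is about 0.4-0.6 exposure SDs for a true AUC of 0.65-0.80. It is wider for weaker associations: about 0.7 at AUC 0.60 and about 1.0 with no association.

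**Larger samples.** At n = 100, event share 30% and AUC 0.70, sensitivity is 0.703 against 0.630 (0.073 too high) and specificity 0.669 against 0.637 (0.032 too high). The bias shrinks but remains.

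**The case against.** The strongest reply is that this is one sentence in a condensed article. It does not say outright that threshold and performance come from the same patients, nor that a correction will be left out, and such details may stand in a full protocol or analysis plan that is not shown. That caveat stands. What keeps the point alive is that the sentence describes a procedure which, followed as written, gives optimistic figures.

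Four further objections also stand and limit the point:
- The 50 per PKI is a minimum for pharmacokinetics, not a size set for the ROC analysis. The 51 is an interim count, and recruitment to this part continued to December 2021.
- The article already concedes that "the number of blood samples may not be sufficient to initiate a population pharmacokinetic analysis for each monitored PKI".
- Exposure appears to be modelled as continuous: it is expressed as area under the curve and trough concentration, and no dichotomisation is mentioned for the Cox, logistic or pharmacokinetic-pharmacodynamic analyses.
- The exposure-response work is a secondary objective and is to be explored, although the ROC sentence itself carries no such label. *Enrollment of Participants* says that usual medical procedure is unchanged, so a reader should not infer that participants are managed by these thresholds.

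A reader might also infer that reported performance is roughly double the truth. That does not hold for any measure the article lists: the AUC is unbiased, and true sensitivity exceeds 0.5 in every simulated cell, so doubling it would pass 100%. Doubling appears only in the Youden index, which the article does not name, and only for weak markers: the ratio at n = 50 is 2.3-2.6 at a true AUC of 0.60, 1.75-2.0 at 0.65, 1.5-1.7 at 0.70 and 1.3-1.4 at 0.80.

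**Conclusion.** The point holds in a moderate form. On the natural reading, the threshold and its sensitivity and specificity are estimated in the same patients with no internal validation. At about 50 patients per drug this overstates sensitivity by about 0.06-0.16 and specificity by about 0.03-0.09, and leaves a cut-off that is uncertain by about 0.4-0.6 exposure SDs when there is a reasonably strong association. These sizes rest on the assumed event shares, true AUC, Youden criterion and normal exposure; other inputs would change them, but not the direction of the bias. The AUC of a single exposure measure is not affected by choosing a cut-off. Severity is minor, because the analysis is secondary and largely exploratory and an unseen analysis plan may already deal with it.

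**What to change.** In the ROC plan, state the criterion for choosing the cut-off. Report bootstrap optimism-corrected or cross-validated sensitivity and specificity, with the whole cut-off search repeated in each resample. Give a bootstrap confidence interval for the cut-off. Label any threshold hypothesis-generating until it is confirmed in other patients, and keep the continuous-exposure models as the main exposure-response analysis, as appears to be intended. The AUC needs no correction for the choice of cut-off.

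The cost is a little extra analysis code, no new data, and less favourable reported performance. If the full protocol or analysis plan already specifies internal validation, a sentence saying so is enough.

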#### Missing Data

Missing data will not be imputed but will be clearly identified and considered during the analysis process (nature and frequency) and described in the publication.

#### Patient and Public Involvement

Patients or the public will not be involved in the design, conduct, reporting, or dissemination plans of this research. The participants will be informed about the study results after the final publication using lay language.

## Results

The first patient was included in May 2015. Until June 2021, 262 patients have participated in at least one part of the study (250 patients have given at least one blood sample, and 130 have been included in the adherence study). In June 2021, 51 patients treated with palbociclib have provided at least one blood sample, and the adherence study currently includes 43 participants with breast cancer, which corresponds to most of the included participants. Moreover, so far, at least one blood sample has been collected from patients treated with 31 different PKIs and their combination (Multimedia Appendix 4).

Data collection is in process, and the final analysis will be performed in 2022. The results of the study will be submitted to local, national, and international conferences and to peer-reviewed open access journals for publication.

## Discussion

### Strength of the Study

The OpTAT study is based on a mixed methodology involving a randomized controlled medication adherence study, along with pharmacokinetic and pharmacodynamic data collection. The methodology is robust, as adherence data will be assessed through electronic monitoring, often considered the gold standard, in both the intervention and control groups. Participants randomized to the intervention group will be included in a routine medication adherence program (IMAP) that has previously been shown to lead to significant improvements in terms of medication adherence; clinical outcomes; and retention in care of other chronically ill patients, such as those with HIV [13,14,37-39]. Moreover, the association between longitudinal adherence and clinical data as well as quality of life and beliefs about medicines through questionnaires will be explored, and the literature in this area is scarce.

The second strength of this study is the pharmacokinetic analysis of a wide range of PKIs. PKIs are marketed under a single regimen according to *the one dosage fits all patients* paradigm, which may be an important source of side effects that are potentially detrimental to the continuation of the course of the treatment and patient adherence. Hence, our ultimate and cutting-edge development is to combine an analysis of PKI adherence, pharmacokinetics, and pharmacodynamics.

### Limitations of the Study

This study has some limitations. First, the adherence data will be collected over 12 months, a time frame during which several stops and breaks in the treatment regimen can occur. This will be a challenge for data analysis; however, the adherence team and the statistician, who will perform the analysis, have already dealt with this kind of data and are experts in this field [14]. Second, we expect some variability in the frequency of adherence visits among participants. Indeed, the adherence interviews are scheduled after each patient’s clinical appointment, and the frequency can vary from a quarterly to a monthly visit depending on the organization of the clinic and the severity of the patient’s disease. Third, the use of an electronic monitor can introduce a Hawthorne effect during the first 6 weeks of the study, which disappears afterward [40]. This effect is explained by the fact that patients who know they are being observed may improve their usual medication behavior. The impact of this effect will be explored in the analysis. Fourth, the number of blood samples may not be sufficient to initiate a population pharmacokinetic analysis for each monitored PKI. All limitations will be considered while analyzing the results and will be detailed in the final publication.

### Conclusions

The OpTAT study will strengthen knowledge on the effectiveness of the routine IMAP medication adherence program in patients with solid cancers treated with PKIs. The IMAP will enable interprofessional teams to learn about patients’ needs and concerns about their PKI self-management. The study will also shed light on PKI pharmacokinetics and its relationship with pharmacodynamic properties, with the aim of adapting dosage regimens at the individual patient level, increasing the clinical suitability of PKIs.

Adherence combined with pharmacokinetic data will inform pharmacists and clinicians on how to support patients during the entire course of their PKI treatment and how to manage adaptations of treatment efficiently, with the patient as an informed partner.

## Appendix

Multimedia Appendix 1 Peer-review reports from the Scientific Office of the Swiss Cancer League/Swiss Cancer Research.

Multimedia Appendix 2 SPIRIT (Standard Protocol Items: Recommendations for Interventional Trials) checklist completed for the optimizing oral targeted anticancer therapies protocol.

Multimedia Appendix 3 Schedule of enrollment, intervention, and assessments of the optimizing oral targeted anticancer therapies study.

Multimedia Appendix 4 Protein kinase inhibitors and their combination included in the optimizing oral targeted anticancer therapies study.

## Abbreviations

CHUV: Lausanne University Hospital
EMERGE: European Society for Patient Adherence, Compliance, and Persistence Medication Adherence Reporting Guideline
IMAP: Interprofessional medication adherence program
OpTAT: Optimizing oral targeted anticancer therapies
PKI: Protein kinase inhibitor
REDCap: Research Electronic Data Capture
SPIRIT: Standard Protocol Items: Recommendations for Interventional Trials
